### Power Analysis and Sample Size

Our sample size estimates were calculated conservatively. Based on the estimates of a risk ratio of 1.75 and the proportion (3.72%) of the control arm who quit smoking (216/5811) in a recent meta-analysis of brief advice interventions [45], we calculated an estimated proportion (6.50%) of the intervention arm who received the brief tobacco intervention and quit tobacco use. We are conducting a cluster RCT with practice settings as the unit of random assignment. Assuming an intraclass correlation of 0.01 and the potential pool of practitioners to be 131, we will need about 36 tobacco-using patients for each practitioner to have a total sample size of 2344 tobacco users per arm, based on a type I error rate of 0.05 and 80% statistical power. Thus, our proposed final sample size is 4688, accounting for 20% attrition among practitioners and 30% among patients. Our effect size estimate is conservative in light of a recent study suggesting a 12.5% quit rate at 6 weeks among smokers receiving behavioral counseling in a pre-post comparison without a control arm receiving standard care in India [9]. Although the 6-month quit rate tends to be lower than the 6-week quit rate after brief advice, we expect our conservative sample size estimate should provide adequate statistical power.

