### Conclusions

Given the low-resource and high-reach nature of the intervention, LifeFirst SWASTH could move the needle on tobacco cessation among marginalized groups. Simple brief advice programs have been shown to have an impact of 1%-3% increased cessation rates over no advice, which could translate to 7.8-23.4 million fewer tobacco users in India [45,46]. Programs such as LifeFirst SWASTH that incorporate further counseling are expected to be even more impactful.

In 2022, for the first time, nicotine replacement medications were added to the Indian Ministry of Health and Family Welfare’s List of Essential Medicines, marking an important step in the effort to address tobacco use in India. Ultimately, this will allow insurance to cover the medications, and generally, access will increase [10,47]. However, some medications, such as additional pharmacotherapies (bupropion, varenicline, and others) that would benefit smokeless tobacco users, were not included in the list [10]. Brief advice and counseling interventions such as LifeFirst SWASTH do address smokeless tobacco use and will pave the way for interventions to include both behavioral and pharmacotherapeutic components by preparing the system to support both in tandem.

Furthermore, this study has the potential to promote health equity. It is a free intervention that is primarily delivered over the phone, minimizing the burden for lower-SES patients. It will advance the implementation science literature by focusing exclusively on lower-SES populations and identifying ways to tailor implementation strategies to meet their unique needs [48].

LifeFirst SWASTH, if found to be effective in terms of cessation outcomes and implementation processes, has the potential to be scaled to other settings in India and other LMICs. The study will be conducted in low-resource settings that will reach many patients, which will increase the impact if demonstrated to be effective and then scaled. It will use task-shifting and a mobile app that can be tailored to different settings, also enabling scalability. Additionally, its findings will build the literature for translating EBIs from high-income countries to LMICs and from high- to low-resource settings.

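### The 80% power is derived with the practitioner as the cluster although sites are randomised, so it leaves out correlation between practitioners at the same site

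*Protocol article*

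**What the plan says.** The Power Analysis and Sample Size section of the protocol article names the randomised unit: "We are conducting a cluster RCT with practice settings as the unit of random assignment". The Randomization section agrees that sites are allocated.

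The planning inputs are given in the same paragraph: "Based on the estimates of a risk ratio of 1.75", "the proportion (3.72%) of the control arm who quit smoking (216/5811") and, from these, "we calculated an estimated proportion (6.50%) of the intervention arm". The calculation is "based on a type I error rate of 0.05 and 80% statistical power". It assumes one intraclass correlation of 0.01, with no level named, and then moves to practitioners: "potential pool of practitioners to be 131, we will need about 36 tobacco-using patients for each practitioner". The result is 2344 per arm and 4688 in total, after allowing for 20% attrition of practitioners and 30% of patients.

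Three other places bear on whether site and practitioner are the same unit:

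- Randomization stratifies on clinic size, measured partly by how many providers a clinic has.
- Compensation Details pays NGO sites a fixed sum for each practitioner who takes part.
- Recruitment and Retention describes dental practices as run by the dentist, who is the practitioner.

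The section on data collection and analysis plans GEE with robust standard errors, with patients clustered within practitioners.

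**The concern.** In a cluster trial, both the design effect and the standard error must carry the correlation among all patients who were allocated together. Here these are the patients of a site. If a site holds several practitioners and their patients resemble each other more than patients of other sites do, a calculation at practitioner level counts too much information.

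Two things are at stake. The power against which a null result will be read may be lower than stated. And if the analysis ignores the site, its standard errors may be too small, so that a positive result looks firmer than it is.

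**Working it through.** **Inputs from the article.** p1 = 0.0372, p2 = 0.065, difference 0.0278, alpha 0.05 (sidedness not stated; two-sided reproduces), power 80%, ICC 0.01, 36 patients per practitioner (4688/131 = 35.8), retention 0.8 × 0.7 = 0.56.

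**1. Reproduce the stated figure.** With mean proportion 0.0511, √(2 × 0.0511 × 0.9489) = 0.3114 and √(0.0372 × 0.9628 + 0.065 × 0.935) = 0.3108. Then

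n = (1.96 × 0.3114 + 0.8416 × 0.3108)² / 0.0278² = 984 per arm.

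- With 36 patients per practitioner, the design effect is 1 + 35 × 0.01 = 1.35, and 984 × 1.35 / 0.56 = 2372. The plan has 2344, a difference of 1.2%.
- With retained patients per practitioner (36 × 0.7 = 25.2), the design effect is 1 + 24.2 × 0.01 = 1.242. The continuity-corrected n is about 1054, and 1054 × 1.242 / 0.56 is about 2340.

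The article does not say which route was taken. Every variant found to reproduce the figure has the practitioner as the cluster, and none contains a site term.

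**2. Power with one practitioner per site.** Retained per arm: 2344 × 0.56 = 1313. On a consistent post-attrition basis the effective n is 1313 / 1.242 = 1057, and

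power = Φ[(0.0278 × √1057 − 1.96 × 0.3114) / 0.3108] = Φ(0.944) = 82.7%.

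**3. Add the site.** For s practitioners per site (equal sizes), m = 25.2, correlation 0.01 within a practitioner and ρ between patients of different practitioners at one site:

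design effect = 1 + (m − 1) × 0.01 + (s − 1) × m × ρ.

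Neither s nor ρ is in the article, so both are assumptions. ρ = 0.01 is an upper case, because it makes patients of two practitioners as alike as patients of one.

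| s | design effect, ρ = 0.005 | power | design effect, ρ = 0.01 | power |
|---|---|---|---|---|
| 1 | 1.242 | 82.7% | 1.242 | 82.7% |
| 2 | 1.368 | 79% | 1.494 | 75% |
| 3 | 1.494 | 75% | 1.746 | 69% |
| 5 | 1.746 | 69% | 2.250 | 58% |
| 10 | 2.376 | 56% | 3.510 | 41% |

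**4. Break-even.** Power is 80% when the design effect is 1313 / 984 = 1.334. This requires (s − 1) × ρ to be no more than (1.334 − 1.242) / 25.2 = 0.0037. So ρ can be at most about 0.0037 with 2 practitioners per site, 0.0018 with 3 and 0.0009 with 5.

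**5. The analysis.** With s = 5 and ρ = 0.005 the true design effect is 1.746, while practitioner-level clustering allows for about 1.242. The standard error is then too small by a factor of √(1.242 / 1.746) = 0.84. This is an illustration under the same assumptions.

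All figures use the normal approximation. Few sites or unequal site sizes would lower power further.

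**The case against.** The strongest reply is that the power calculation matches the planned analysis, since both cluster on practitioners, and that its arithmetic is sound. That is true, but the agreement does not help: under site randomisation both leave out the same correlation, and the analysis would then tend to understate standard errors.

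A second reply is that the article never says that NGO sites have several practitioners. This stands in part. The size stratum and the payment per practitioner make it likely without giving a number, the flow diagram is not available here, and in dental practices the site may be a single dentist. Practitioner attrition would also shrink sites.

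Stronger readings are tempting, but the article does not support them:

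- A reader might infer that power is really 70%, 61%, 49% or 33% for 2, 3, 5 or 10 practitioners per site. Those values combine the retained sample with the cluster size before attrition (36) and apply the full 0.01 across the site. On a consistent basis the starting point is 82.7%, which leaves a little slack.
- A reader might infer that the 80% is simply wrong. It could still hold if nearly all sites have one practitioner or if the site-level correlation is very small.
- A reader might dispute "Our sample size estimates were calculated conservatively" because the planned 2.78 points lie near the top of the range in "Simple brief advice programs have been shown to have an impact of 1%-3% increased cessation rates over no advice". The Conclusions go on to expect more from programmes that add counselling, as this one does, so the wording is arguable and not an error.
- The eligibility range of 10 to 60 patients per practitioner describes recruiting capacity and is not a distribution of cluster sizes. Little can be built on it.

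**Conclusion.** The concern holds as a mismatch of level. Sites are randomised, while 2344 per arm and 80% power follow from practitioner clusters with no allowance for correlation between practitioners of one site. The direction is clear: any such positive correlation lowers power below the single-practitioner value.

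The size is uncertain. It ranges from a loss of about 4 points (2 practitioners per site, ρ = 0.005) to about 42 points (10 per site, ρ = 0.01) from the base of 82.7%, under assumed site sizes and correlations. A mix that includes single-dentist practices would lose less than the table shows for the same NGO site size. The article does not establish that the trial is underpowered; it does not support the 80% for the design as randomised.

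**What to change.** In Power Analysis and Sample Size, state the actual number of sites, the patients per site and how much these vary. Practitioner recruitment is complete, so the site list is known. Restate power and the detectable difference over a range of site-level correlations, for example 0.005 to 0.02. No further patients need be enrolled.

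In the analysis section, cluster the GEE robust standard errors on the randomised site instead of the practitioner, with a small-sample correction if sites are few.

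The cost is one rewritten paragraph and one changed line in the model specification. The stated power becomes less favourable, and standard errors may be somewhat larger.

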### Informed Consent

During their initial in-person training, study staff will review the consent form with practitioners and obtain written consent. Practitioners will take preliminary verbal consent from patients who are interested and eligible and document it in the app. The counselors and data collectors will be able to view patients who have provided preliminary consent. During the first phone call with the patient, the NSF counselor or data collector will review the participation consent form with the referred patients over the phone and answer any questions. The institutional review board (IRB) has granted us a waiver of written consent for the patients, given that they will be interacting with the counselors and data collectors over the phone. After the 6-month follow-up call, if a patient has been randomly selected for cotinine testing, the counselor or data collector will double-check that they still consent to the test. The NSF team will use data from the app to document who has provided consent. It will be made clear during the consent process that all participants (practitioners and patients) may decide not to participate at any time with no consequences.

### Privacy and Confidentiality

All identifiable data will be securely stored with the NSF team. They will remove the data of any identifiable information and save the deidentified data in password-protected Cloud-based files. Only deidentified data will be used for analysis. Urine specimens collected for the cotinine tests will be stored securely by the lab conducting the tests in Mumbai, India, for 48 hours after collection.

### Compensation Details

All study participants will receive small monetary incentives to express our appreciation for their participation. Practitioners will receive INR 500 (about US $6) for completing each of the following activities: attending training, registering each patient, completing a 3-month posttraining follow-up survey, and completing a 6-month posttraining follow-up survey. Patients will receive INR 500 (about US $6) when they register for the study, INR 200 (a little over US $2) for completing each of the 1-week, 1-month, and 3-month follow-ups, and INR 500 (about US $6) for completing the 6-month follow-up. The patients who undergo cotinine testing will also receive INR 500 (about US $6) for completing the test. Each of the health and TB NGO sites will receive a one-time payment of INR 10,000 (about US $120) per practitioner participating to account for overhead costs. Given that the dentist practitioners operate their own practices, they will not receive a site-level incentive. These amounts were selected based on the NSF team’s past experiences delivering similar programs to ensure that the amounts are enough to be meaningful to the study populations but not coercive.

### Additional Considerations

All patients in both intervention and control arms will be provided with a pamphlet on the ill effects of tobacco use. Although this is not a “standard of care” in India at this time, it is a common intervention and also accounts for ethical requirements given the degree to which the patients are marginalized and underserved.

No generative language models have been used in this project or this paper.

### Ethical Considerations

This study was approved by the Harvard Longwood Campus IRB in Boston (IRB19-0562) on April 25, 2019, and the Joint Ethics Committee for Narotam Sekhsaria Foundation and Salaam Bombay Foundation in Mumbai (JEC/NSF-SBF nAl9lOS) on August 5, 2019. It is registered in ClinicalTrials.gov of the US National Institutes of Health and in the Clinical Trials Registry of India.

## Results

Recruitment for the RCT commenced in November 2023. As of July 2024, 102% (135/132) have been recruited and trained, including both the intervention and control arms of all 3 setting types. The 3 extra practitioners trained will provide additional help to address attrition; recruitment and training of practitioners are complete. Approximately 36% of patients (1687/4688) have been registered. The first follow-up has been completed for 93% (1460/1574) of the eligible patients; the second follow-up has been completed for 90% (1089/1204) of the eligible patients; the third follow-up has been completed for 87% (583/667) of the eligible patients; and the fourth follow-up has been completed for 76% (188/248) of the eligible patients.

## Discussion

### Principal Findings

In terms of effectiveness outcomes, it is hypothesized that those patients who participate in the adapted LifeFirst SWASTH program will be more likely to have been abstinent from tobacco for 30 consecutive days at the final (6-month) follow-up compared to those patients in the control arm. Furthermore, the patients assigned to the intervention arm will have decreased their tobacco use, even if they did not quit entirely, compared to those in the control arm at the 6-month follow-up.

There are several limitations to be noted. Although 20% of the subsample will provide biomarker-verified cessation outcomes, the majority of patient-level cessation outcomes will be based on self-report. This allows for the possibility of social desirability bias, as tobacco users may under-report their use. Loss to follow-up, especially in low-resource community settings, remains a limitation that may result in potential bias in missing data for engaging patients for follow-ups and outcome measures. While randomization at the cluster level is an effective approach to mitigate potential contamination, it is possible that even a large cluster RCT may not result in a balance of patient-level characteristics between the 2 arms. Selection bias at both patient- and health care provider or practice levels could affect the causal rigor in ascertaining the trial effect. This trial aims to recruit a large sample of current tobacco users across multiple low-resource clinical settings. The large samples of both health care providers and patients yield important information about the delivery and receipt of the intervention, which will eventually affect tobacco cessation. The longitudinal design involving both short- and long-term follow-ups and repeated measures of tobacco cessation outcomes including biomarker verification on a subset of patients will advance our understanding of both proximal and distal effects of this trial. Longitudinal analysis of these repeated-measures outcomes will elucidate the impact of this pragmatic cessation trial on the behavioral trajectories of tobacco use severity and cessation outcomes.

### Conclusions

Given the low-resource and high-reach nature of the intervention, LifeFirst SWASTH could move the needle on tobacco cessation among marginalized groups. Simple brief advice programs have been shown to have an impact of 1%-3% increased cessation rates over no advice, which could translate to 7.8-23.4 million fewer tobacco users in India [45,46]. Programs such as LifeFirst SWASTH that incorporate further counseling are expected to be even more impactful.

In 2022, for the first time, nicotine replacement medications were added to the Indian Ministry of Health and Family Welfare’s List of Essential Medicines, marking an important step in the effort to address tobacco use in India. Ultimately, this will allow insurance to cover the medications, and generally, access will increase [10,47]. However, some medications, such as additional pharmacotherapies (bupropion, varenicline, and others) that would benefit smokeless tobacco users, were not included in the list [10]. Brief advice and counseling interventions such as LifeFirst SWASTH do address smokeless tobacco use and will pave the way for interventions to include both behavioral and pharmacotherapeutic components by preparing the system to support both in tandem.

Furthermore, this study has the potential to promote health equity. It is a free intervention that is primarily delivered over the phone, minimizing the burden for lower-SES patients. It will advance the implementation science literature by focusing exclusively on lower-SES populations and identifying ways to tailor implementation strategies to meet their unique needs [48].

LifeFirst SWASTH, if found to be effective in terms of cessation outcomes and implementation processes, has the potential to be scaled to other settings in India and other LMICs. The study will be conducted in low-resource settings that will reach many patients, which will increase the impact if demonstrated to be effective and then scaled. It will use task-shifting and a mobile app that can be tailored to different settings, also enabling scalability. Additionally, its findings will build the literature for translating EBIs from high-income countries to LMICs and from high- to low-resource settings.

## Abbreviations

5A’s framework: ask, advise, assess, assist, and arrange framework
CHW: community health worker
EBI: evidence-based intervention
GATS-2: 2016-2017 Global Adult Tobacco Survey
IRB: institutional review board
LifeFirst SWASTH: LifeFirst Supporting Wellbeing among Adults by Stopping Tobacco Habit
LMIC: low- and middle-income country
MMR: Mumbai Metropolitan Region
NGO: nongovernmental organization
NSF: Narotam Sekhsaria Foundation
PPA: point prevalence abstinence
RCT: randomized controlled trial
SES: socioeconomic status
TB: tuberculosis
WHO: World Health Organization
